## 3. Discussion

In relation to the first endpoint, we expect that patients with MCI due to AD will show significantly more SN deficits than healthy controls and individuals with SCD, both in the AppleGame and in the DNT-mv, in terms of higher drop errors on BPI, LPI, and PPI and higher amounts of WTs and MsH, respectively. Virtual and ecological deficits may reflect a cognitive inefficiency of the entorhinal cortex, where AD neuropathology manifests early [25]. It has also been demonstrated that virtual and ecological SN tasks can detect the SN alteration of amyloid-positive MCI patients [89,90]. According to Colmant et al. [91], we also presume that APOE-ε4 carriers will report a PPI deficit in the VR task differently from non-carriers, regardless of subgroup.

Furthermore, we also anticipate that significant physiological parameters modifications (particularly, respiratory function) may be particularly associated with MsH, given that anxiety rather than depression significantly influences SN abilities in non-demented elders [92]. Starting from difficulties in spatial orientation evaluated in naturalistic experiments able to modify gait [93], we finally assume that patients with MCI due to AD will perform worse than SCD and healthy controls in terms of “Time” and “Speed”, and report significant differences in “Direction”, all variables collected by the Howdy Aptive app in the open-space naturalistic task.

In relation to the second endpoint of the research, we assume that the drop errors obtained in the VR task may predict the route disorientation scores of the naturalistic task. In particular, we expect a causal relationship between the BPI drop error of the AppleGame and the *Route A* return path of the DNT-mv, as well as between the LPI drop error of the AppleGame and the *Route B* return path of the DNT-mv, because they mainly rely on egocentric and on allocentric navigation, respectively. A recent systematic review and meta-analysis [44,94] has outlined that the association of navigational tasks performed in virtual and real environments needs to be deeply clarified. In light of this, we believe that the AppleGame could represent a validated technique with which to detect, in laboratory, early SN deficits in populations at risk of dementia conversion to provide high-quality, time-limited diagnosis. It is a cost-effective tool able to predict real-life SN impairment that should be routinely used in clinical practice.

However, our research protocol presents some limitations. Urban park conditions (e.g., presence of potential distractors) might influence the performance of the study participants in the naturalistic task, and the technology used may breaks down in relation to the GPS signal power. Moreover, the frequency of APOE-ε4 carriers, especially in patients with MCI due to AD, may be unsatisfactory due to specific demographical variables of our European country [95]. Although the APOE-ε4 represents the strongest genetic risk factors for AD [54], as genetic research has proceeded, studies have found suggestive links between late-onset AD and a number of other genes, such as ABCA7, CLU, CR1, PICALM, PDL3, TREMZ, and SORL1 [96,97], which might be relevant in influencing SN performances, too.

Nevertheless, we first estimate the impact of the present research project in terms of an innovative technological SN assessment in senior citizens at high risk of developing AD dementia, with relevant implications for maintaining independent spatial orientation in daily life activities. In fact, this kind of smart technological apparatus (i.e., a body T-shirt with sensorial devices and a smartphone with digital health Apps) is able to alert caregivers when their loved ones with cognitive decline are required to navigate unfamiliar locations alone, and it constitutes a potential means of remotely monitoring them.

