### 2.4. Statistical Analysis

Data distribution will be first checked on collected variables by assessing skewness and kurtosis values, by performing normality and heteroscedasticity tests, and by visually inspecting histogram and Q–Q plots. Based on data meeting or non-linear model assumption, either parametrical or non-parametrical analyses will be performed. By means of the R marco *pwr* [86], the minimal sample size has been set as 76 participant, based on a power analysis for a multiple regression model that took into account the following parameters: α = 0.05; 1-β = 0.9; *f*^2^ = 0.15 (medium effect size, in order to be conservative) [87]; and numbers of predictors: 3 (age, APOE genotypes, and belonging to each group, with the last two predictors as dummy variables).

We will detect the route disorientation scores, i.e., WTs and MsH, as already described in Puthysserypaddy et al. [64]. Accordingly, all the violations in terms of deviations from the pre-established return path (i.e., movement at an intersection onto a different path as compared to the original one, or non-roadable walkways) will be written down by the experimenter as WTs in a pre-set paper grid for *Route A*. The overlaps with the *Route A* return path, and, likewise, non-roadable walkways will be written down by the experimenter as WTs in a pre-set paper grid for Route *B*. Further, we will detect the MsH as the participant either slows down/stops and looks around to aid orientation or verbally admits to the experimenter that he/she is unsure about his/her whereabouts, both for *Route A* and the *Route B* return path.

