In addition to the experimenter visually identifying and recording the frequency of the MsH with a stopwatch and a pre-set paper grid, we will measure this variable more objectively using the Howdy Senior integrated accelerometer. For this purpose, we will use the motion sensor of the sensorial body measuring the individual’s linear acceleration in the three axes (i.e., x, y, z). To segment the magnitude signals, according to Schaat et al. [88], we will adopt time intervals of 10 s, with an overlap of 5 s between subsequent intervals because a 10 s segment is sufficiently long to capture multiple steps during walking, thus revealing important behavioral changes. In this way, we will detect the MsH as a signal flattened along the three axes. Further, given that physiological parameters may alter depending on the MsH, we will also investigate the relationship between step variability and co-occurring time-dependent cardiac and respiratory parameters detected by the Howdy App, expressed as mean values, via Pearson’s correlation coefficients or their non-parametric equivalent (i.e., Spearman’s rank order correlation). Moreover, we will run a one-way ANOVA (or its non-parametric equivalent) to compare performances of the three subgroups on gait parameters collected through the Aptive app and the SSNC questionnaire. In order to explore potential association between specific neurocognitive functions and SN impaired abilities, Pearson correlations or their non-parametric equivalent (i.e., Spearman’s rank order correlation) will be further performed between the AppleGame/DNT-mv results and the neuropsychological tests used in the sending centers, especially visual–constructive skills and executive functions (see Appendix A). Given the difference of the neuropsychological battery used in the sending centers, we will group tests according to the primary cognitive domain involved and we will divide the scores obtained in a dichotomous way for each participant according to the reported cut-off values in the test manuals, i.e., 0 = pathological performance; 1 = normal performance.

Finally, a linear/generalized linear regression analysis will be run, taking into account the drop errors of the AppleGame subtasks—considered one at a time—as independent variables, and the total number of “wrong turns” (WTs)/total number of “moments of hesitation” (MsH) (in seconds) of the DNT-mv as dependent variables.

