The Howdy Senior system has been recently implemented by the “Aptive” App capable of recording GPS data during the naturalistic experiment. These data include “Time” as the number of minutes to complete the route; “Latitude”, “Longitude”, “Altitude”, and “Speed” as estimated by the body integrated accelerometer for calculating steps variability; and “Direction” corresponding to gait orientation with values ranging from 0° to 360°, where 0° corresponds to the north, 90° to the east, 180° to the south, and 270° to the west. Thanks to the Aptive App, a GPX tracking of participants’ body movements around the urban environment will be registered, too.

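### Time to complete the route includes hesitation and wrong-turn time, so a group difference in it does not show that gait has changed

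*Protocol article*

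**What the plan says.** All places are in the protocol article.

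- **Time and Speed.** The text on the Aptive App after Table 1 defines Time "as the number of minutes to complete the route". It does not remove stops or off-route walking. It lists Speed "as estimated by the body integrated accelerometer for calculating steps variability" and does not say how the readings are summarised over the route.
- **Hesitation.** Section 2.4 says "we will detect the MsH as the participant either slows down/stops and looks around to aid orientation", or when the participant voices uncertainty. This is scored on the return paths of Routes A and B. The sensor version comes from the same wearable: "we will detect the MsH as a signal flattened along the three axes". The closing regression takes WTs and "MsH) (in seconds) of the DNT-mv as dependent variables".
- **Wrong turns.** Section 2.4 scores deviations from the return path on Route A, and overlaps with Route A on Route B. Walking off the permitted paths counts on both.
- **Planned comparison.** Section 2.4 compares the three groups on the Aptive gait parameters by one-way ANOVA or a rank-based alternative. It states no moving-only version and no adjustment for MsH or WTs.
- **Expectation.** The Discussion first expects MCI to be worse on WTs and MsH. It then assumes that "patients with MCI due to AD will perform worse than SCD and healthy controls in terms of" Time and Speed, and introduces this with "Starting from difficulties in spatial orientation evaluated in naturalistic experiments able to modify gait".

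**The concern.** The Discussion's premise is that disorientation changes how people walk. Time cannot test that premise. Someone who walks normally but stops to look around, or takes a wrong path and corrects it, takes longer to finish. Those stops and detours are already scored as MsH and WTs. If MCI patients differ only in those two scores, Time moves in the predicted direction by construction, and a significant result labelled as a gait parameter could be read as altered gait. As planned, nothing in the comparison separates slower walking from more stopping or a longer path.

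**Working it through.** The plan gives no design figure for this comparison. The sample size of 76 is for a regression model and has no bearing here.

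**Inputs from the article.** Route A is L = 80.5 m (section 2.3.2), and its return uses the same route. Groups are 25 healthy, 25 SCD and 26 MCI (Abstract).

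**Assumptions, because the article gives no values.** Walking speed s averages 1.0 m/s (0.8 to 1.2 in the single-person check), with a between-person SD of 0.15 to 0.20 m/s. Hesitation h is in seconds and gamma-distributed with shape 1.0 to 1.5. Detour d is in metres. Hesitation is treated as standing still. Where a participant only slows, the added time is less than the scored seconds.

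**Formulas.**
- Time = (L + d)/s + h
- Path speed averaged over the whole walk = (L + d)/Time
- Nominal length over Time = L/Time
- Moving speed = s

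**One participant, s = 1.0 m/s, moving speed unchanged throughout.**

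| h (s) | d (m) | Time (s) | Change in Time | Path speed (m/s) | L/Time (m/s) |
|---|---|---|---|---|---|
| 0 | 0 | 80.5 | – | 1.00 | 1.00 |
| 10 | 0 | 90.5 | 10/80.5 = +12% | 80.5/90.5 = 0.89 | 0.89 |
| 20 | 0 | 100.5 | 20/80.5 = +25% | 80.5/100.5 = 0.80 | 0.80 |
| 0 | 20 | 100.5 | +25% | 100.5/100.5 = 1.00 | 0.80 |

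At 0.8 to 1.2 m/s, 20 s of stops raises Time by 20 to 30% (20/100.6 to 20/67.1). The last row shows that a detour lengthens Time but leaves a speed measured along the path unchanged.

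**Three groups with identical true walking speed.** These are simulated one-way ANOVAs at the 5% level, 2,000 to 3,000 runs per setting, with mean hesitation of 5 s in healthy and SCD and no detours. The ranges cover the assumed SD and gamma shape.

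| MCI mean hesitation | Time rejects |
|---|---|
| 10 s | 13–22% |
| 15 s | 37–63% |
| 20 s | 65–90% |

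- Kruskal–Wallis gives 12–22%, 35–59% and 59–86% for Time, so the planned rank-based alternative does not remove the problem.
- A whole-route average speed behaves much like Time: 14–20% at 10 s and 63–79% at 20 s (gamma shape 1.0).
- With a mean detour of 20 m in MCI only and no hesitation, Time rejects in 87–98% of runs and path speed in 4–5%.
- Moving speed rejects in 4–6% of runs, the nominal level.

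**If Time also covers an outward leg.** The outward Route A walk is guided and has no scored hesitation. Including one such leg makes the base 2 × 80.5 = 161 s, so 10 to 20 s of stops adds 10/161 = 6% to 20/161 = 12%. Among runs where the MsH comparison is itself significant (gamma shape 1.5), Time then rejects in 9%, 25% and 45% (SD 0.15) or 7%, 14% and 27% (SD 0.20) for MCI means of 10, 15 and 20 s.

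**The case against.** **Completion time is a legitimate navigation measure.** Section 1.7 treats the wearable data as part of comparing navigation performance, and a measure that includes getting lost is valid for that purpose. This stands, and is a reason to keep Time. It does not justify reading Time as gait.

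**Speed is not Time in another form.** A reader might infer that Speed is the reciprocal of Time, so that one quantity is reported twice, or that wrong turns lower Speed. The article does not support this. Speed is a sensor estimate with no stated summary. Stops lower it only if it is averaged over the whole route, and detours would lower it only if it were nominal length divided by Time, which the article does not say. The summary may be set in the full protocol.

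**A positive MsH result does not settle the Time result.** A reader might infer that it nearly guarantees one. Among simulated studies with a significant MsH comparison (gamma shape 1.5, return leg only), Time is significant in 24%, 63% and 90% at MCI means of 10, 15 and 20 s with SD 0.15, and in 15%, 39% and 70% with SD 0.20. The overlap is real, but its effect depends on how much more MCI patients hesitate.

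**The article does not claim independent confirmation.** It derives the expectation for Time and Speed openly from disorientation and asserts no separate motor deficit. To say that it counts the same stops again as new evidence goes beyond the text.

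**Moving speed has its own limits.** MsH includes slowing, so removing MsH segments also removes some of the gait change that the authors expect. The 10 s windows with 5 s overlap are coarse for a walk of about 80 s. Both points stand, and they argue for adding moving speed and against replacing Time with it.

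**Conclusion.** The point holds for Time, by the article's own definitions. On the legs where MsH and WTs are scored, Time contains hesitation and detour time, so a group difference in it cannot show that disorientation modifies gait. The possible distortion ranges from modest to large: little more than the nominal error rate at 5 s of extra mean hesitation with variable walking speed, and up to 90% rejection at 15 s extra with unchanged walking. It is smaller if the timed route includes unscored outward legs, which the article leaves open. For Speed the point is conditional on a whole-route average. The sizes rest on assumed speeds, hesitation times and distributions. The overlap itself does not. The sample size and the second endpoint are unaffected.

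**What to change.** In section 2.4 and the Aptive App text:

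1. Keep Time, describe it as a navigation-performance measure that overlaps with MsH and WTs, and state which legs it covers. Report it split into moving time, hesitation time and detour time.
2. Add moving speed, meaning accelerometer or GPX speed outside MsH segments, and use it for any statement about gait. State how Speed is summarised.
3. State that Time, or a Speed averaged over the whole route, will not be read as evidence of gait change separate from MsH and WTs.

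The cost is a short derivation from signals already recorded and a few sentences of text, with no new data. Removal of stops will be approximate because of the 10 s windows, and slowing scored as MsH drops out of moving speed. Moving speed should therefore be reported beside Time and not in place of it.

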The human navigation system naturally encourages the strategic translation of egocentric and allocentric information and the use of path integration. People ordinarily use egocentric navigation strategies during visual–spatial tasks such as walking a familiar route many times [6]. The egocentric navigation strategy is self-centered and involves the encoding of spatial information in relation to the position of the navigator. It is also based on different cues, allowing individuals to navigate as follows: perpetual processing of visual landmarks by bodily movements (e.g., “Turn left at the church”, “Turn right at the supermarket”, and then “Go straight to the pharmacy”), an endogenous integration of sensorimotor stimulation, vestibular information, and self-motion [6]. By contrast, when people travel a novel route, egocentric spatial representations are not available, and world-related navigational strategies are employed (i.e., allocentric navigation). They allow individuals to mentally represent a “cognitive map” of the environment based on the relationships among landmarks. This navigation strategy is also referred to as “wayfinding” [7]. Remarkably, they permit the travelling of alternative routes to come back to the starting point [6]. Further, when people are able to use urban environmental landmarks, they can successfully navigate thanks to the translation of spatial information from allocentric to egocentric strategies and vice versa (e.g., “I am 20 m from the pharmacy” and “The pharmacy is to the right of the supermarket”) (cf., [6]). Path integration, which is based on idiothetic cues, is the ability to transform internal information into a sense of location and orientation [8]. Self-motion cues (vestibular, proprioceptive, and motor information) are combined together to allow individuals to continuously estimate their position and orientation in space [9]. When participants walk blindfolded and with ear plugs, or when the environmental information is removed (with the exception of the optic flow alone), for example, in virtual reality tasks, it is possible to isolate idiothetic information from allothetic information [10]. Allothetic navigation, in turn, uses landmarks and boundaries to successfully navigate the environment [11], and pure allothetic navigation can be detected through desktop-based virtual reality tasks only [12]. Pure path integration (PPI) is particularly important because it permits the estimation of distances and the navigation of environments without using boundaries and landmarks. PPI can be studied both in virtual tasks, providing the navigator with a scenario bare of boundaries and landmarks (Figure 2), and in real-world settings thanks to the use of idiothetic indexes, as in the case of the triangle completion task [10]. However, in our daily experience, path integration and allothetic strategies are used jointly to derive location and direction. Some studies have shown that providing allothetic information during path integration tasks or vice versa can improve people’s orientation ([8,13,14]).

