### 1.2. Neural Correlates of Spatial Navigation

Advances in the investigation of neural correlates of human SN have shown that a large network of cognitive mechanisms, supported by different brain areas, is involved (Figure 3). The cerebral areas sub-serving egocentric and allocentric strategies interact with specific brain cells supporting SN, i.e., head direction (HD) cells, grid cells, boundary cells, and place cells (PC). The anterodorsal thalamic nucleus—included in Papez’s circuit—contains a large proportion of head direction (HD) cells [18] informing the individual as to in which direction he/she is heading. They maximally fire when the head of the person is facing in a specific direction with respect to the surrounding environment [18]. Grid cells are neurons of the entorhinal cortex that exhibit firing fields as triangular patterns tiling the environment [19]. Boundary cells, discovered in the medial entorhinal cortex, too, fire in response to fixed boundaries in the surrounding space, contributing to analyzing the limits of the environment [20]. The hippocampal formation in both rats and humans is involved in spatial navigation [21], and spatial memories are thought to be encoded and retrieved in the hippocampus through the activity of place cells [22]. Place cells fire when an animal visits specific regions of the environment, or “place fields” [23]. Specifically, hippocampal CA1 and CA3 place cells in the medial temporal lobe provide allocentric mental representations [24]. According to Puthusseryppady [25], novel environments are first encoded as egocentric representations by the parietal cortex. As one person continues to move within the environment, the HD cells and the grid cells provide information for brain path integration. The egocentric representations are then transformed into the allocentric representations by the retrosplenial cortex and the parietal-occipital sulcus, and this is combined with information provided by the boundary cells in order to generate and store “cognitive maps” in the hippocampus via the place cells. However, in other cognitive domains, such as executive functions, attention and working memory may play a critical role in SN performance [26].

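### The Discussion expects boundary performance to match Route A and landmark performance to match Route B, but the one-at-a-time models on total scores cannot separate such specificity from one shared navigation ability

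*Protocol article*

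**What the plan says.** Section 1.7 sets the second endpoint: whether performance on the laboratory task predicts impairment in a real-world setting. Section 3 (Discussion) adds a narrower expectation: "we expect a causal relationship between the BPI drop error of the AppleGame and the" Route A return path, and likewise between the LPI drop error and the Route B return path, "because they mainly rely on egocentric and on allocentric navigation, respectively".

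Section 2.4 (Statistical Analysis) gives the model: a linear or generalized linear regression "taking into account the drop errors of the AppleGame subtasks—considered one at a time—as independent variables", with "the total number of “wrong turns” (WTs)/total number of “moments of hesitation” (MsH) (in seconds) of the DNT-mv as dependent variables". That sentence mentions no split by route, no joint model and no comparison between subtasks. The same section does record wrong turns on separate grids for each route, and moments of hesitation when the participant slows, looks around or says "that he/she is unsure about his/her whereabouts, both for" Route A and the Route B return. Section 2.3.2 labels Route A predominantly egocentric and Route B predominantly allocentric.

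**The concern.** The Discussion's expectation is about pairs: BPI belongs with Route A and LPI with Route B. To support it, the predicted pairs must be stronger than the crossed pairs (BPI with Route B, LPI with Route A). Section 2.3.1 describes all three AppleGame subtasks as path integration tasks that differ only in the supportive cues offered, so a common component is built in. A model with one drop error in it cannot tell that common component from something specific to the boundary or the landmark.

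Two significant predicted pairs could therefore be reported as egocentric and allocentric correspondence, even as a causal link, when the data would look the same if people who navigate well simply do well on everything. If the totals in Section 2.4 pool the two routes, the route-specific expectation is not tested at all.

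**Working it through.** **Inputs from the article.** N = 76, alpha 0.05 and f² = 0.15 (Section 2.4). No correlation between AppleGame and DNT-mv scores is given, so all loadings below are assumptions.

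**The plan's own figure.** Recomputing the sample size with its stated inputs (3 predictors, f² = 0.15, power 0.90) gives 99, not 76; 76 gives 79.6% power. None of those three predictors is a drop error, so the calculation does not bear on this point. N = 76 is used only as the number of participants.

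**Step 1: shared ability only.** Let g be one navigation ability. Each subtask score is X = λx·g + √(1 − λx²)·e and each route score is Y = λy·g + √(1 − λy²)·e, with independent noise and no pair-specific link. Every subtask–route correlation, predicted or crossed, is then r = λx·λy.

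**Step 2: one-at-a-time tests by route.** With Fisher's z, the chance that one pair is significant is about Φ(atanh(r)·√73 − 1.96).
- r = 0.5 × 0.5 = 0.25: Φ(0.255 × 8.544 − 1.96) = Φ(0.22) = 0.59; squared, 0.35.
- r = 0.7 × 0.5 = 0.35: Φ(0.365 × 8.544 − 1.96) = Φ(1.16) = 0.88; squared, 0.77.
- r = 0.8 × 0.5 = 0.40: Φ(0.424 × 8.544 − 1.96) = Φ(1.66) = 0.95; squared, 0.91.

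Squaring treats the two pairs as independent, so it was checked by simulation (several thousand data sets per setting; repeat runs moved results by about a percentage point):

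| Loadings (subtask/route) | Both predicted pairs significant | Both crossed pairs significant |
|---|---|---|
| 0.5/0.5 | 36% | 36% |
| 0.7/0.5 | 78% | 78% |
| 0.8/0.5 | 91% | 91% |

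As an anchor, f² = 0.15 in a single-predictor model means R² = 0.15/1.15 = 0.13, or r = 0.36. At that correlation (loadings 0.6/0.6) both predicted pairs are significant in 82%.

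**Step 3: a test aimed at specificity.** Under Step 1, Cov(BPI − LPI, A − B) = (λBPI − λLPI)(λA − λB). This is zero if either the two subtasks or the two routes load equally. In a joint model with PPI, BPI and LPI, the BPI-minus-LPI slope contrast on standardised A minus standardised B is significant in about 5% of data sets in every setting above.

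A contrast within one route is less safe. With BPI loading 0.8 and LPI 0.6 (PPI 0.7, routes 0.5), it is significant in about 11% without any specificity, while the A-minus-B contrast stays near 5%.

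**Step 4: power of the A-minus-B contrast.** Add a pair-specific component to each predicted pair (general loadings 0.7/0.5). Power is about 25% for a specific loading of 0.3 and 61% for 0.4.

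**Step 5: the labels.**
- BPI as egocentric. Section 1.2 says the egocentric representations are transformed into allocentric ones and "this is combined with information provided by the boundary cells in order to generate and store “cognitive maps” in the hippocampus". That puts boundary information on the allocentric side. Section 1.1 describes egocentric cues as landmark-guided turns and "an endogenous integration of sensorimotor stimulation, vestibular information, and self-motion", with no mention of boundaries.
- LPI as allocentric. Section 1.1 builds the cognitive map on relations among landmarks, while LPI offers one landmark; landmarks also appear as an egocentric cue. This is loose, but not a clear contradiction.

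**The case against.** Five points on the other side have weight.

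- **The endpoint is general prediction.** Section 1.7 asks only whether laboratory performance predicts real-world impairment. Single-predictor models address that, and a shared ability would be a genuine positive answer. This stands in full. A reader might infer that the second endpoint is invalid; the article does not support that.
- **Cue type is not reference frame.** It is tempting to argue from "Allothetic navigation, in turn, uses landmarks and boundaries to successfully navigate the environment" that both subtasks must be allocentric. Section 1.1 also says that self-motion and environmental cues can each support either frame, so allothetic does not mean allocentric. Section 1.2 is a general neural account in which path integration feeds the map too. The subject of the quoted clause in the Discussion could even be the two return paths. So the mapping as a whole is not contradicted; only BPI as egocentric fits poorly.
- **PPI is not left out.** Section 2.4 covers all the AppleGame subtasks, so PPI is modelled against the real-world outcomes. It lacks only a route-specific prediction. Pairing it with Route A would swap one unproven mapping for another.
- **The matched-pair rates assume route-level outcomes.** Section 2.4 names totals. If these pool the routes, the rates do not apply as a description of the plan, but then the Discussion's expectation is not tested, which is no better.
- **The size is assumption-driven.** Lower loadings give lower rates (about 18% at 0.5/0.4), and the simulation uses correlations where wrong turns are counts. The equality of predicted and crossed pairs does not depend on the size of the loadings.

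**Conclusion.** The point holds in a limited form. The analysis stated in Section 2.4 cannot support the route-specific expectation in the Discussion, and observational single-predictor regressions cannot support the word causal. Under a shared ability only, at N = 76, both predicted pairs would be significant in about 36% to 91% of data sets for loadings from 0.5/0.5 to 0.8/0.5, with crossed pairs significant as often. The range rests on assumed loadings, roughly normal scores and route-level outcomes.

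General prediction, the second endpoint as Section 1.7 defines it, is not affected. BPI as egocentric needs a justification or should go; LPI as allocentric is not clearly contradicted. This is not detail that an article may leave to a fuller plan, because the article states both the pair-specific expectation and a model that does not test it.

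**What to change.** - Keep the one-at-a-time models in Section 2.4 for general prediction, and say that this is their purpose.
- For the Discussion's expectation, use Route A and Route B scores separately; they are already recorded. Fit standardised PPI, BPI and LPI drop errors jointly. Test the BPI-minus-LPI slope contrast on standardised Route A minus standardised Route B, with its confidence interval.
- Report all six subtask–route pairs.
- Claim route-specific correspondence only if the contrast supports it in the predicted direction. Otherwise conclude only that virtual performance is associated with real-world performance.
- In Section 3, replace the causal wording with association, and justify or drop the egocentric label for BPI. Do not add a PPI–Route A pairing as a new hypothesis.

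The cost is wording and one further model per outcome (wrong turns, hesitation) on data already planned. There are two limits. Power is modest at N = 76 (about 25% to 61% for assumed specific loadings of 0.3 to 0.4), so a null contrast should be reported as inconclusive on specificity. By the Step 3 formula, the contrast is not exactly zero under a shared ability if the subtasks and the routes both load unequally; differences of 0.2 in each give 0.2 × 0.2 = 0.04. The six reported pairs let a reader judge that.
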